**Figure 1 F1:**
[figure not shown]
Flow diagram showing the trial decision guidelines for the run-in period of the trial design, incorporating a conventional 3+3 cohort design if dose escalation is required.

If results from the first cohorts show an acceptable DLT rate (see later) and trough levels of BTT1023 meet the stipulated success criteria, the trial will continue into the expansion component of the trial. Acceptable trough levels have been set a trough concentration of 3 μg/mL free circulating BTT1023 at 8 weeks from first infusion, which is approximately 100-fold the dissociation constant (K_d_) of BTT1023 from VAP-1 and will result in target occupancy of approximately 90%. In the event that DLT rate is acceptable but the PK levels do not meet the success criteria, then the trial moves into a conventional 3+3 cohort design, using escalating doses of BTT1023. In this event, the original cohort of 6 patients will no longer be evaluated, but a new cohort of 3 patients will be recruited to receive the newly identified test dose of 12 mg/kg. If there are no DLTs at Visit 10 [Day 99], an additional cohort of 3 patients will be recruited at the new test dose. If the DLT rate remains acceptable but the PK levels still do not meet the success criteria, a further 3+3 patients will be recruited at the highest dose of 16 mg/kg. If this is found not to result in sufficient blood levels of BTT1023, then the trial will be stopped. If the PK values are found to be too high (such as resulting in trough levels consistently exceeding 100 μg/mL), then there is potential to de-escalate the dose in agreement with the Data Monitoring Committee (DMC) and after regulatory approvals. The trial will be stopped at any stage where patient safety is compromised. Individual patients will only receive one dose level. Once a confirmed dose has been established, the trial will expand until a total of 37 patients have received treatment with the confirmed dose, including those patients who have previously received this dose during the confirmatory period. Those patients not receiving the confirmed dose will not be included in the final evaluation.

### Patient selection

Patients with particularly elevated ALP levels are predicted to be more at risk of progressive disease; thus, these patients will be selected. Currently, four UK academic hospital centres are involved (based in Birmingham, Nottingham, Oxford and Newcastle) with further centres potentially coming on board shortly. Informed consent will be obtained by appropriately trained members of the research team at each site.

The main inclusion criteria are patients aged 18–75 years with a clinical diagnosis of PSC, as evidenced by chronic cholestasis of more than 6 months duration with either an MRI or liver biopsy consistent with PSC and in the absence of a documented alternative aetiology. Patients must have an ALP of at least 1.5 times the upper limit of normal. Those with concomitant IBD must have evidence to show clinically and colonoscopically stable disease within the past 12 months, without findings of high-grade dysplasia and without the need for biological therapies. In those on treatment with ursodeoxycholic acid (UDCA), therapy must be stable for at least 8 weeks prior to screening and at a dose not greater than 20 mg/kg per day. In those not on treatment with UDCA at the time of screening, a minimum of 8 weeks since the last dose of UDCA should be recorded. As an IgG molecule, BTT1023 is not anticipated to interfere with chromosomal material; however, teratogenicity has not been studied and so rigorous steps will be taken to exclude pregnancy pre-treatment and with regard to need for effective contraception throughout the trial and for 99 days after. Some of the main exclusion criteria can be seen in box 1.Box 1Main exclusion criteria (not a complete list)AST and ALT >10xULN or bilirubin >3xULN or INR >1.3 in the absence of anti-coagulants.Serum creatinine >130 μmol/L or platelet count <50 x 109/L.Any evidence of hepatic decompensation past or present, including ascites, hepatic encephalopathy or variceal bleeding.Recent cholangitis within last 90 days or ongoing need for prophylactic antibiotics.Pregnancy or breast feeding.Flare in colitis activity within last 90 days requiring intensification of therapy beyond baseline maintenance treatment; use of oral prednisolone >10 mg/day, biologics (ie, monoclonal antibodies) and or hospitalisation for colitis within 90 days. Prior use of biologics is not a contraindication to screening.Diagnosed cholangiocarcinoma or high clinical suspicion of cholangiocarcinoma.Concurrent malignancies or invasive cancers diagnosed within past 3 years except for adequately treated basal cell and squamous cell carcinoma of the skin and in situ carcinoma of the uterine cervix.Presence of a percutaneous drain, bile duct stent or prior organ transplantation.Participation in an investigational trial of a drug or device within 60 days of screening or 5 half-lives of the last dose of investigational drug.Positive screening test for tuberculosis (TB) (including T-SPOT.TB TB test), unless respiratory review confirms false-positive test results.Receipt of live vaccination within 6 weeks prior to baseline visit.

## Treatment

A single-arm, rather than placebo-controlled, design was chosen to allow efficient enrolment of patients into the study due to its intensive nature, in which a significant chance of being allocated into the placebo group may act as a substantial barrier for enrolment. The proposed primary endpoint (ALP) is a biochemical measurement and thus not open to subjective bias as a clinical assessment would be, rendering the necessity of a concurrent control group less vital.

## Trial schema

Given the unpredictable nature of PSC and natural variation of ALP levels, we have built into the trial a two-stage screening process over 4–7 weeks, whereby the ALP levels must not vary by more than 25% in order to continue to enrolment. During screening, patients have routine blood screens and other non-invasive markers of liver fibrosis including Mayo PSC Risk Score, MELD, Enhanced Liver Fibrosis (ELF), Fibroscan and MRCP with additional LiverMultiscan imaging. These will then be repeated during treatment and in the follow-up period to assess for any change.

During all 7 treatment visits, patients will receive pre-medication with cetirizine 10 mg + ibuprofen 400 mg orally (in the absence of any contraindications) plus intravenous hydrocortisone 100 mg, 1–2 hours pre infusion (the latter for the first 3 doses only). The first infusion will be given over 2 hours, with a 4-hour monitoring period post infusion. Provided that no adverse reactions are seen, the infusion time will drop to 1 hour with initially a 3-hour observation period (for the second dose) and then down to 2 hours monitoring post infusion (for all subsequent doses). Safety investigations will be completed pre infusion and post infusion and they include haematology/biochemistry sampling, along with ECG, clinical assessment and physical examination. The full trial schema can be seen as figure 2.

**Figure 2 F2:**
[figure not shown]
BUTEO trial schema.

A aliquot (0.5–1.0 mL) of the BTT1023 infusion solution will be taken at the end of every infusion and refrigerated. These samples may be used for analysis of BTT1023 concentration if anomalies in PK data are observed that could be due to errors in IMP preparation.

### Data analysis plan

#### Power calculations and sample size justification

The dose confirmatory stage requires a maximum of 18 patients. The sample size has been based on the classic 3+3 design, investigating three fixed dose increments (8, 12 and 16 mg/kg), with no dose skipping.

The expansion phase follows a Simon’s two-stage minimax design with lower and upper acceptability bounds of 15% and 30%, respectively, and error rates α=0.10 and β=0.20. Thirty-seven patients are required in this stage of the trial; however, to account for patient dropout, estimated at approximately 10%, the sample size is extended by a further 4 patients. As such, the target recruitment is up to 41 patients for the expansion phase and up to 59 participants in total. An interim assessment will examine the primary outcome once 18 evaluable patients have been recruited at the confirmed dose. If 3 or more responses are observed in stage 1, then the trial will continue into stage 2. Recruitment will not be halted while stage 1 is assessed. If the stage 1 criterion is not met, then the trial will cease. However, if the criterion is met, then further patient recruitment continues until 37 evaluable patients are recruited. If overall there are 9 or more responses from 37 evaluable patients, then we conclude that the treatment warrants further investigation.

In this setting, the interpretation of alpha (α) is the probability satisfying stage 1 and observing 9 or more responses in 37 patients overall when the true response rate is 15%; a false-positive result (type 1 error). Beta (β) is the probability of failing to acknowledge activity when the true response rate is 30% (type 2 error). As such, the power, 1−β, is the probability of taking an effective treatment forward.

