## Interim analysis

An interim analysis will be completed once 18 patients have been evaluated for the primary outcome (ALP response). If 3 or more responses are observed, then the trial will continue. If this is not met, then the trial will cease. If adequate response is seen, a further 19 patients will be recruited in order to obtain the required sample size of 37 patients (allowing for 10% patient dropout during trial duration, this number could reach a total of 41 patients recruited). The final success criterion chosen maintains power and, in doing so, can incur an increased type 1 error rates (note that the stage 1 criterion is fixed since the final sample size is unknown at stage 1). These have been calculated by the trial biostatistician and independently verified by a Cancer Research UK Clinical Trials Unit biostatistician.

Patients that cannot be evaluated for the primary outcome (eg, due to withdrawal or lost to follow-up) will be treated as non-responders.

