### Final analyses

Final analyses of the primary outcome will be performed when all patients have been followed to Day 120 and once the database has been locked. If overall there are 9 or more responses from 37 evaluable patients, then we conclude that the treatment warrants further investigation. Only patients treated at the confirmed dose will contribute to the total patient requirement.

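### The final decision is set on 37 evaluable patients, but one section ends accrual at 37 treated and another counts non-evaluable patients as non-responders

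*Protocol article*

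**What the plan says.** The protocol article describes the expansion phase as a "Simon’s two-stage minimax design with lower and upper acceptability bounds of 15% and 30%, respectively", with α of 0.10 and β of 0.20. Four sections bear on who is counted at the end.

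- **Power calculations and sample size justification.** Stage 1 is 18 evaluable patients, with 3 or more responses needed to go on. After that: "However, if the criterion is met, then further patient recruitment continues until 37 evaluable patients are recruited". On dropout: "to account for patient dropout, estimated at approximately 10%, the sample size is extended by a further 4 patients", which gives 41.
- **Final analyses.** "If overall there are 9 or more responses from 37 evaluable patients, then we conclude that the treatment warrants further investigation".
- **Study design overview** (paragraph after the Figure 1 legend). "the trial will expand until a total of 37 patients have received treatment with the confirmed dose".
- **Interim analysis.** After 37 is named as the required number, "this number could reach a total of 41 patients recruited". On the cut: "The final success criterion chosen maintains power and, in doing so, can incur an increased type 1 error rates". On missing outcomes: "Patients that cannot be evaluated for the primary outcome (eg, due to withdrawal or lost to follow-up) will be treated as non-responders".

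**The concern.** Two of these statements do not fit the decision rule.

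If expansion ends at 37 treated patients, anyone who withdraws before the Day 99 ALP is already inside the 37. The 4 extra patients are then never recruited, and 37 evaluable patients can be reached only with no dropout at all.

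If patients who cannot be evaluated are scored as non-responders in the decision, every treated patient has an outcome. The word evaluable then excludes nobody, and adding patients to replace dropouts has no clear purpose. The sentence stands under the interim heading, but withdrawal affects both looks and nothing says which analysis it governs.

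This is the trial's only formal efficacy decision. It is taken in an open-label single arm, where one response can tip it. If the denominator is settled after ALP results are known, the stated error rates no longer describe the decision.

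**Working it through.** **Inputs.** From the sample-size section: p0 = 0.15, p1 = 0.30, stage 1 n1 = 18 with at least 3 responses, final n = 37 with at least 9, dropout about 10%, at most 41 recruited. Two assumptions are added: dropout is independent of response, and 15% and 30% are the rates in evaluable patients.

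**Formula.** Exact two-stage binomial:

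P(success) = Σ over x from 3 to n1 of Bin(x; n1, p) × P[Bin(n − n1, p) ≥ 9 − x].

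Where withdrawals count as non-responders, p is replaced by p(1 − d). At d = 0.10 this is 0.30 × 0.90 = 0.27 and 0.15 × 0.90 = 0.135.

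**Step 1: the plan's own design.** A full minimax search over sizes and cuts returns exactly 18/37 with 3 and 9. Power is 80.6% and type I error 8.7%, so the stated design is correct when 18 and 37 evaluable patients are counted.

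**Step 2: the other readings at 10% dropout, cut 9.**

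| Who is counted | Power | Type I error |
|---|---|---|
| 37 evaluable | 80.6% | 8.7% |
| 41 treated, withdrawals as non-responders, stage 1 = first 18 treated | 77.8% | 8.4% |
| 41 treated, withdrawals as non-responders, stage 1 = first 20 treated | 79.7% | 8.8% |
| 37 treated, withdrawals as non-responders at both looks | 68.2% | 5.1% |

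The last row gives power of 74.9% at 5% dropout and 60.7% at 15%.

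**Step 3: do 41 treated secure 37 evaluable?** On average they almost do: 41 × 0.90 = 36.9. With binomial dropout, the chance of fewer than 37 evaluable is 5% at 5% dropout, 39% at 10% and 76% at 15%.

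**Step 4: what a shortfall does.** With the cut held at 9, power is 78.2% at 36 evaluable and 68.9% at 33. The highest cut that keeps 80% power at 33 to 36 is 8. It gives power of 80.3% (at 33) to 86.3% (at 36), with type I error of 10.6% to 14.9%. This matches what Interim analysis describes: power held, type I error allowed to rise.

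**Step 5: sensitivity to the assumption about withdrawals.** Suppose withdrawals are all true non-responders and 15% is the rate among all treated.

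- The rate in evaluable patients is then 0.15 / 0.90 = 16.7%, and the false-positive rate with 9 of 37 evaluable is 14.4%.
- Counting all 41 with a cut of 9 is not immune to this: at a 15% rate over all 41 counted patients the false-positive rate is 13.7%. The 8.4% to 8.8% in the table depends on 15% being the rate in evaluable patients and on about 10% dropping out.

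**The case against.** The strongest reply is that the decision rule is stated twice and identically, in the sample-size section and in Final analyses. The recruitment ceiling of 41 also appears in two sections. The sentence in Study design overview is an accrual summary with no success criterion, and the non-responder sentence may concern only the interim look or a descriptive rate. Much of this stands: the weight of the text favours 37 evaluable patients with dropouts added on top. It does not remove the problem, because an accrual rule that stops at 37 treated contradicts that plan as written, and nothing limits the non-responder sentence to one analysis.

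Three stronger readings are tempting and are not supported.

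- *The trial has only 68% power.* That needs the accrual stop at 37 treated, the non-responder rule and an unchanged cut of 9, all together. No section states the combination, and Interim analysis says the final cut is chosen to maintain power.
- *80% power is lost unless exactly 37 are counted.* With the cut of 9, 38 to 41 evaluable patients give power of 82.7% to 87.5%. What rises is type I error, from 9.9% to 13.7%.
- *No cut exists for a shortfall.* Interim analysis says the calculations for this were made and independently verified. The article condenses a fuller protocol that may list them, so their absence here is no finding.

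It is also fair to say that keeping withdrawals as failures is a defensible, conservative choice in a single-arm trial. Dropping that rule from the decision is a trade-off, not a correction.

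**Conclusion.** The point holds as a contradiction between stated rules. The sample-size section and Final analyses agree on 9 of 37 evaluable with up to 41 recruited. The accrual sentence in Study design overview conflicts with them, and the scope of the non-responder rule is left open.

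The size depends on which sentences are followed. If 41 are recruited and withdrawals count as failures, the loss is small: 80.6 − 79.7 = 0.9 to 80.6 − 77.8 = 2.8 points of power. The loss reaches about 12 points (80.6 − 68.2 = 12.4) only in the three-part combination described above. These figures assume 10% dropout independent of response, with 15% and 30% as rates in evaluable patients. The matter should be corrected, but it does not undermine the design, whose stated operating characteristics reproduce exactly.

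**What to change.** In Study design overview, replace the stop at 37 treated with accrual to 37 evaluable patients, up to 41 treated. Then state one denominator, with its cut, for both looks. Two choices are coherent.

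- **(a) Decide on evaluable patients.** Use 3 of 18 and 9 of 37, and confine the non-responder rule to a supporting response rate over all treated patients. If 41 treated yield fewer than 37 evaluable, apply the power-maintaining cuts that Interim analysis says were calculated, fixed before the data are seen. The cost is a higher false-positive rate if withdrawals are really non-responders: 14.4% at 37 evaluable.
- **(b) Keep withdrawals as non-responders in the decision.** Recruit 41, require 9 of 41, say whether stage 1 is the first 18 or the first 20 treated, and restate power as about 78% to 80%. The cost is about 1 to 3 points of power. The type I error should be restated with its dropout assumption, since it reaches 13.7% if nobody drops out or if 15% is the rate over all treated.

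Neither option needs patients beyond the 41 already planned. The choice is the sponsor's, and it should be made before any Day 99 responses are reviewed.

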## Outcome measures and analysis

This is an early-phase trial of BTT1023 in immune cell mediated liver disease, with the rationale to identify biochemical efficacy (reduction in ALP) and safety, in an orphan disease that presently lacks any other effective medical therapy. The trial design therefore focuses on identifying early biochemical efficacy signals to justify larger-scale, randomised controlled trials of a longer duration.

Our primary outcome measure is patient response to treatment at Day 99, and it is a reduction in serum ALP by 25% or more from baseline to Day 99. Our data on stability of ALP in PSC suggests that such responses occur very seldom during the natural course of the disease, and we can therefore reliably assess changes from baseline and response rates for this proof of concept study to evaluate the therapeutic potential of BTT1023. In addition, we are excluding patients in whom the levels change significantly naturally by >25% in the 5-week to 7-week screening period.

Secondary outcome measures include safety and tolerability via treatment compliance, patient withdrawal, frequency of serious adverse event (SAE)/adverse event (AE), change in quality of life questionnaires (EQ-5D, Fatigue Severity Scale, Pruritus Visual Analogue Score, Inflammatory Bowel Disease Diaries) and change in quality of BTT1023 efficacy (via tests of liver fibrosis including ELF, Fibroscan and liver biochemistry). Additionally, liver MRI is an emerging method for monitoring liver disease and its treatment. We will evaluate changes in MRI imaging pre therapy and post therapy using the LiverMultiscan protocol (or equivalent methodology, at sites where this is possible). Finally, we will evaluate changes in sVAP-1/SSAO as a biomarker of liver disease activity across the study period.

## Interim analysis

An interim analysis will be completed once 18 patients have been evaluated for the primary outcome (ALP response). If 3 or more responses are observed, then the trial will continue. If this is not met, then the trial will cease. If adequate response is seen, a further 19 patients will be recruited in order to obtain the required sample size of 37 patients (allowing for 10% patient dropout during trial duration, this number could reach a total of 41 patients recruited). The final success criterion chosen maintains power and, in doing so, can incur an increased type 1 error rates (note that the stage 1 criterion is fixed since the final sample size is unknown at stage 1). These have been calculated by the trial biostatistician and independently verified by a Cancer Research UK Clinical Trials Unit biostatistician.

Patients that cannot be evaluated for the primary outcome (eg, due to withdrawal or lost to follow-up) will be treated as non-responders.

### Final analyses

Final analyses of the primary outcome will be performed when all patients have been followed to Day 120 and once the database has been locked. If overall there are 9 or more responses from 37 evaluable patients, then we conclude that the treatment warrants further investigation. Only patients treated at the confirmed dose will contribute to the total patient requirement.

## Adverse event reporting

### Dose-limiting toxicity

Dose-limiting toxicity (DLT) is defined as an AE that meets the criteria of grade 3 cytokine release syndrome or grade 4/5 for any criteria, as defined in the Common Terminology Criteria for Adverse Events (CTCAE V4.0). Although previous studies have shown no DLTs with BTT1023, toxicity monitoring will be ongoing throughout the trial and any concerns will be reported to the Trials Office within 24 hours of the investigator becoming aware of the event. The DLT reporting period is from Visit 3 (first infusion) to Visit 10 (21 days after last infusion). An acceptable DLT rate has been established for the trial as a maximum of 1 incidence in 6 patients (~17%). If the DLT rate rises to 2 or more, at any stage during the DLT reporting period (Visit 3 [Day 1] to Visit 10 [Day 99]), the trial will be halted in consultation with the DMC.

### Adverse events/serious adverse events

The collection and reporting of AEs will be in accordance with the Medicines for Human Use Clinical Trials Regulations 2004 and its subsequent amendments. The CTCAE V4.0 criteria will be used to grade each AE. Any pre-existing conditions will be reported in the medical history and will not be reported as an AE unless the condition worsens by at least one CTC grade during the trial. The reporting period for AEs will commence from the date of consent (Visit 1) and will continue until the final follow-up visit (Visit 11: Day 120) or alternatively up to 45 days post last infusion if the patient withdraws from the study prior to completion of all 7 study drug infusions. All trial patients will continue to receive standard concomitant clinical care throughout the study.

The Sponsor, appropriate regulatory authority (eg, Medicines and Healthcare Products Regulatory Agency (MHRA)) and the Research Ethics Committee (REC) will be informed of all SAEs as required by current regulations. An SAE judging to have a reasonable causal relationship to the drug will be recorded as a serious adverse reaction or a suspected unexpected serious adverse reaction, as appropriate, and will be reported to the MHRA and REC within 7 days. The independent DMC will also review all SAEs.

In the event that a patient or their partner becomes pregnant during the SAE reporting period, this will be recorded and reported and followed up, subject to required patient/partner approvals.

